##### Sampling of endometrial tissue

The endometrial samples of infertile patients with moderate/severe IUA were obtained under hysteroscopy. Some of the samples were immersed in 4% paraformaldehyde and fixed for 24 h, while others were frozen rapidly in liquid nitrogen and stored at −80°C for later use.

##### Paraffin embedding and section preparation of sample tissues

These procedures included the following: (1) tissue gradient dehydration, (2) tissue clarification, (3) wax infiltration, (4) embedding, and (5) sectioning. The sections were floated in warm (45°C) water in a spreading machine, picked up with slides once the tissue had been fully flattened, baked at 60°C, removed 2 h later, and stored at a normal temperature (25°C) for later use.

##### Masson’s staining

This procedure involved the following steps: (1) dewaxing and hydration, (2) hematoxylin nuclear staining, (3) Ponceau staining, (4) treatment with phosphomolybdic acid, (5) aniline blue staining, (6) differentiation, (7) dehydration and clarification, (8) mounting, and (9) optical microscopy, image collection, and analysis.

##### Determination of endometrial cell proliferation

To determine whether the ECM could promote endometrial cell proliferation, Ki67 immunohistochemical staining was conducted. Von Willebrand factor immunohistochemical staining in the endometrial injury region was conducted to observe the regeneration and distribution of microvessels in the endometrium. At a magnification of ×40, the proliferative cell count of three fields was randomly selected and averaged.

#### Frozen embryo transfer after thawing

Patients were given 4 mg of exogenous estrogen on the 2nd/3rd day of menstruation at a maximum dose of 8 mg for a total of 15–20 days. When the endometrial thickness was ≥7 mm, progesterone was given for endometrial transformation, and embryo transfer was generally performed on days 20–22. Three-dimensional ultrasonography was performed to evaluate the endometrial thickness and morphology, intrauterine volume, endometrial VFI, FI, VI, and uterine artery blood flow resistance. Between 1 and 2 high-quality embryos were transplanted. Blood beta (β)-hCG and progesterone were measured 14 days after embryo transplantation. At 35 days after embryo transfer, B-scan ultrasonography was performed to check the clinical pregnancy status.

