**Methods:**

This paper presents a prospective randomized single-blind controlled superiority study of infertile women aged ≤40 years with IUA. According to the scoring criteria for IUA established by the American Fertility Society, patients with moderate or severe IUA were randomized into two groups at a ratio of 1:1; patients in the experimental group were treated with an ECM scaffold (small intestinal submucosa [SIS]) + intrauterine balloon, while patients in the control group were treated with an intrauterine balloon only. A hysteroscopic examination of adhesion repair was performed again after 2 months of postoperative hormone replacement therapy. Endometrial tissue was sampled during the two operations, and immunohistochemistry was used to observe endometrial and microvascular proliferation. After thawing and resuscitation, a postoperative frozen embryo transfer was performed on the participants in both groups, and their endometrial thickness, intrauterine volume, endometrial vascularization flow index, endometrial flow index, and uterine artery blood flow resistance were evaluated by 3D ultrasonography. The rates of embryo implantation, clinical pregnancy, and early spontaneous abortion were observed.

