### Screening of infertility patients with intrauterine adhesions

Patients with infertility with secondary hypomenorrhea were evaluated by 3D ultrasound for endometrial thickness and morphology on days 3–7 after menstruation, and the intrauterine volume, endometrial vascularization flow index (VFI), endometrial flow index (FI), and endometrial vascularization index (VI) were recorded. According to the patients’ medical history and 3D ultrasound imaging examinations, infertile women aged ≤ 40 years who suffered from IUAs were screened and admitted to the hospital for adhesiolysis. Following admission, the patients were collected for a review of their general circumstances and medical history, which included blood pressure, heart rate, pulse and respiration, menstruation, menstrual and obstetrical histories, past medical history, operation history, and family medical history.

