### Secondary outcome measures

These included the endometrial thickness, menstrual volume, and clinical pregnancy rate.“Endometrial thickness” referred to the anterior and posterior diameter of the endometrium in the longitudinal section of the uterus, which changed with the menstrual cycle. The measurement of endometrial thickness was based on the following: In the median sagittal section of the uterine body, perpendicular to the midline of the endometrium, the maximum thickness diameter was measured between the lateral edges of the double-layer endometrium. If there was uterine effusion, the thickness and diameter of the two monolayers were measured and added to the overall total.The evaluation of menstrual volume is the total amount of bleeding in each menstrual cycle. The normal menstrual volume is 20–60 ml, and more than 80 ml is considered to be excessive. Typically, this is judged by the number of sanitary napkins used. Under normal circumstances, 10–20 sanitary napkins will be used in a menstrual cycle. If the level of menstruation required fewer than 10 sanitary napkins or only one was needed, the amount of menstruation had been reduced. Based on the number of sanitary napkins that were used before the hysteroscopy, if this was more than the amount before the procedure, the amount of menstruation was considered to have increased. If there was no change in the menstrual volume compared with before the procedure, the menstrual volume was considered as having shown no improvement.Blood β-hCG and progesterone were measured 14 days after embryo transfer to evaluate whether a biochemical pregnancy was present. On day 35 after embryo transfer, a vaginal ultrasound showed that there was a gestational sac in the uterus with an embryo and fetal heart beat; this was determined as a clinical pregnancy.Ongoing pregnancy rate = the number of clinical pregnancies ≥12 weeks/the number of embryo transfer cycles × 100%Clinical pregnancy rate = the number of clinical pregnancies/the number of embryo transfer cycles × 100%Embryo implantation rate = the total number of implanted embryos/the total number of transplanted embryos × 100%Ectopic pregnancy rate = the number of ectopic pregnancies/the total number of clinical pregnancies × 100%Early spontaneous abortion rate = the number of spontaneous abortions at a gestational age of <12 weeks/the total number of clinical pregnancies × 100%

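### The only post-operative endometrial thickness reading described lies in a transfer cycle that proceeds at 7 mm or more, so the arms are compared conditional on a threshold that treatment may affect

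*Protocol article*

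**What the plan says.** The protocol article, under Secondary outcome measures, opens its list with thickness: "These included the endometrial thickness, menstrual volume, and clinical pregnancy rate". It defines the measurement anatomically and notes that thickness is a quantity "which changed with the menstrual cycle", but it names no day or cycle for the reading.

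Two occasions for a thickness scan are described.

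- **Before surgery.** Under Screening, patients are "evaluated by 3D ultrasound for endometrial thickness and morphology on days 3–7 after menstruation".
- **After surgery.** Under Frozen embryo transfer after thawing, estrogen is given "at a maximum dose of 8 mg for a total of 15–20 days". The next step is conditional: "When the endometrial thickness was ≥7 mm, progesterone was given for endometrial transformation", and transfer follows. The scan is described after that step: "Three-dimensional ultrasonography was performed to evaluate the endometrial thickness and morphology". The Methods paragraph of the abstract makes the same link: "a postoperative frozen embryo transfer was performed on the participants in both groups, and their endometrial thickness" and the other ultrasound measures were then evaluated.

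The Hysteroscopic re-examination section mentions no thickness scan. A thin endometrium is an inclusion criterion, and the Evaluation criteria describe it as less than 7 mm, the same value at which the transfer cycle proceeds.

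**The concern.** If the analysed value is the one taken in a cycle that has gone ahead, every analysed value is at least 7 mm. Women whose endometrium stays below 7 mm are those in whom repair has done least for thickness, and they have no described reading in the comparison.

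Reaching 7 mm happens after randomisation, and the scaffold is meant to make it more likely. Conditioning on it has two consequences. The two sets of women compared are selected differently by arm, so randomisation no longer protects the comparison. The mean difference among those selected also understates the true one when the two arms have similar spread, because part of the effect moves into the proportion reaching 7 mm and into the estrogen dose or days needed to get there.

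The trial could then report little or no effect on thickness when a real one exists.

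**Working it through.** The article gives no mean, SD, expected difference or power for thickness, so there is no stated figure to reproduce. What follows is an illustration.

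**Inputs from the article.** Threshold 7 mm (Frozen embryo transfer after thawing); 83 women per arm (Sample size, where it serves the primary outcome); two-sided tests at 0.05 (Statistical analysis methods).

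**Assumed inputs.** Thickness on estrogen is normal with the same SD in both arms: SD 1.0, 1.5 or 2.0 mm; control mean 5.5 to 9 mm; true difference 0.5, 1.0 or 1.5 mm.

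**Formulas.** With a = (7 − μ)/σ and λ = φ(a)/(1 − Φ(a)):

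- proportion reaching 7 mm = 1 − Φ(a)
- mean among them = μ + σλ
- variance among them = σ²(1 + aλ − λ²)

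**Worked case: means 6.5 and 7.5 mm, SD 1.5 mm.**

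- Control: a = 0.333, proportion 0.369, λ = 1.0215, mean 6.5 + 1.5 × 1.0215 = 8.03 mm, SD 0.82 mm.
- Scaffold: a = −0.333, proportion 0.631, λ = 0.5985, mean 7.5 + 1.5 × 0.5985 = 8.40 mm, SD 1.00 mm.
- Observed difference 8.40 − 8.03 = 0.37 mm instead of 1.0 mm, a loss of 63%.

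**Power in that case (normal approximation).**

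- All 83 per arm, no threshold: SE = 1.5 × √(2/83) = 0.233, z = 4.29, power 99%.
- Threshold applied: 83 × 0.369 = 31 and 83 × 0.631 = 52 women contribute. SE = √(0.82²/31 + 1.00²/52) = 0.20, z = 1.81, power 44%.
- Threshold applied but 83 contributing in each arm: SE = 0.142, z = 2.58, power 73%.

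The fall from 99% to 44% therefore has two parts: to 73% from the truncation itself, and the rest from fewer contributing women.

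**Same means, other SDs.** The observed difference stays at 0.36 to 0.37 mm. Power with the threshold is 76% at SD 1.0 mm (over 99% without it) and 28% at SD 2.0 mm (90% without it).

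**Share of the true difference lost, over all assumed SDs and differences.**

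| Control mean on estrogen (mm) | Loss |
|---|---|
| 5.5 | 71–83% |
| 6 | 66–77% |
| 6.5 | 57–69% |
| 7 | 44–61% |
| 7.5 | 30–55% |
| 8 | 18–48% |
| 9 | 4–33% |

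More than half is lost in every scenario at 6.5 mm or below and in all but one at 7 mm. It is never more than half at 8 mm or above.

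**Unequal SDs.** With means 6.5 and 7.5 mm but SD 1.0 mm in control and 2.0 mm in the scaffold arm, the means among those reaching 7 mm are 7.64 and 8.79 mm. The difference is 1.15 mm, larger than the true 1.0 mm. The bias towards zero therefore depends on the SDs being similar.

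**The case against.** The strongest reply is that no sentence in the article sets the truncation. The outcome definition names no scan, and nothing says that the post-threshold reading is the endpoint or that lower readings are thrown away. Applying the 7 mm rule requires thickness to be read before the decision, so lower values must exist for women who start the cycle. This stands: a reader might infer an explicit rule to exclude values below 7 mm, and the text contains none. It does not remove the problem, because the only evaluation described comes after the threshold step and nothing says that lower values count.

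A second reply is that the reading day is a detail that a condensed article may leave to the full protocol. A bare omission would not be a finding. Here, however, the article does describe when thickness is evaluated, and that occasion is conditional on the outcome itself. An analysis plan written later could not recover values that were never recorded as endpoint data.

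Three stronger readings should be set aside.

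- That most of any true difference is lost. This depends on the control mean on estrogen, which the article does not give. The description of thin endometrium as under 7 mm concerns women before adhesiolysis, so it makes means near 7 mm plausible but does not establish them.
- That women are treated without limit until they pass the cut-off. The article caps both estrogen dose and duration.
- That the comparison with baseline is invalid because the screening scan, "endometrial thickness and morphology on days 3–7 after menstruation", falls in a different cycle phase. The article specifies no change-from-baseline analysis of thickness; its statistical section describes comparisons between groups.

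**Conclusion.** The point holds as a conditional one. Read naturally, the article compares thickness between women selected by a post-randomisation threshold that treatment may affect, and that is not a comparison of the randomised groups. This part needs no numerical assumption beyond that reading.

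The size does rest on assumptions. With normal values and similar SDs the difference is biased towards zero, by more than half if control means on estrogen are about 6.5 to 7 mm or lower, and by less if they are higher. With clearly unequal SDs even the direction is not assured. The outcome is secondary and the primary outcome is untouched, so this should be corrected but does not threaten the trial's main conclusion.

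**What to change.** Leave the clinical 7 mm rule and the estrogen regimen as they are, and change only what is recorded and compared.

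1. Define the endpoint as thickness at the monitoring scan on one pre-specified day of the first preparation cycle. Record it whatever its value, before the decision to proceed, for every randomised woman who starts that cycle.
2. Add the proportion of all randomised women who reach 7 mm, counting those who never start the cycle as not reaching it.

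The cost is a change of endpoint wording and one recorded value from monitoring that the 7 mm rule already requires. The scan day has to be standardised across women. Those who never start a preparation cycle will still have no thickness value, so the first measure remains a comparison within a post-randomisation subset; the second covers that gap because it keeps every randomised woman in the denominator.

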#### Embryo scoring criteria

The criteria for embryo evaluation at the cleavage stage and embryo scoring were as follows:Grade I: Blastomeres that were uniform in size and free of fragmentsGrade II: Blastomeres that were uniform or slightly uneven in size with fragments < 20%Grade III: Blastomeres that were uniform or slightly uneven in size with fragments <20–50%Grade IV: Blastomeres that were uneven in size with fragments >50%

Grades I and II indicated high-quality embryos, and grades I, II, and III indicated transplantable embryos.2)Blastula evaluation criteria. Blastocysts could be classified as grades I–VI according to the degree of expansion and hatching, as follows:Grade I early blastula: The volume of the blastular cavity was smaller than half of the total volume of the blastocystGrade II blastula: The volume of the blastular cavity was larger than half of the total volume of the blastocystGrade III completely expanded blastula: The blastular cavity occupied the entire lumenGrade IV blastula after expansion: The volume of the blastular cavity was significantly larger than the early blastula, and the zona pellucida was thinnerGrade V incubating blastula: The blastula incubated from the rupture of the zona pellucidaGrade VI hatched blastula: the blastulae emerged completely from the zona pellucida.Grades III–VI blastulae were scored for inner cell mass (ICM) and trophoblast ectoderm cells.

The ICM scores were as follows:Grade A: A large number of cells, binding tightlyGrade B: Fewer cells, binding looselyGrade C: Very few cells

The trophoblast ectodermal cell scores were as follows:Grade A: A large number of cells distributed around the blastocystsGrade B: Fewer cells and relatively loose epithelial cellsGrade C: Very few cells

Blastocysts with a D5 score of ≥3AA, 3AB, 3BA, or 3BB or a D6–7 score of ≥4AA, 4AB, 4BA, or 4BB were identified as high-quality blastocysts.

### Randomization and allocation

Eligible participants will be randomly assigned to the experimental group or the control group in a 1:1 ratio by central randomization performed by an independent statistician from our team. Random numbers are generated by Excel, which will generate a random number table, and the allocation sequence was registered on the Shanghai Shenkang Development Center (https://crip-ec.shdc.org.cn/html/admin/auth/login). According to the random number table, the statistician puts each grouping scheme into an opaque envelope, writes the code on the outside of the envelope, seals it, and gives it to the researcher. Once the hysteroscopic process entered the uterine cavity, the degree of uterine cavity adhesion was evaluated according to AFS. If the uterine cavity was assessed as reflecting moderate or severe uterine cavity adhesion, the itinerant nurse opened the envelope with the corresponding number. Then, the operator intervened according to the grouping scheme in the envelope. The process of unpacking the envelope was time consuming but did not affect anesthesia or hysteroscopy. The researchers were made aware of the distribution following the hysteroscopic surgery.

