Endometrial injury can easily cause IUA, which primarily manifests as an endometrial basal layer injury caused by trauma, infection, and other factors, resulting in the dysfunction of functional endometrial repair; in turn, this will lead to the proliferation of fibrous connective tissue and endometrial fibrosis as well as partial or total intrauterine occlusion [2, 4]. According to the consensus of Chinese experts on the clinical diagnosis and treatment of intrauterine adhesions [5], at present, for patients suffering from infertility, recurrent abortion, and oligomenorrhea and for those with special fertility requirements, transcervical resection of adhesion (TCRA) can be conducted as a preferred treatment (recommendation level: C). Moreover, TCRA combined with an intrauterine device (IUD), Foley balloon support, or estrogen and progesterone replacement therapy has shown degrees of anti-adhesion value, although their effects are variable. An IUD placement after moderate and severe IUA could reduce the formation rate of re-adhesion to 35% [6] (evidence level: I). But meta-analysis showed that the menstrual improvement rate ranged between 28.5 and 100%. Several studies have indicated significant differences in this regard [7]. In addition, although an intrauterine balloon can make the total effective rate of IUA repair reach 71.67% [8] and improve the menstrual rate up to 81.4–95% [9, 10], the shape of the balloon used in clinics is not suitable for the intrauterine cavity, which makes it difficult to block the wound completely. Moreover, if the intrauterine balloon is not placed properly, intimal ischemia and necrosis may occur, which will impact intimal regeneration and repair. In particular, for patients with severe IUA, due to endometrial basal layer damage, reduced residual normal endometrial tissue, and poor regeneration ability, the recurrence rate of postoperative adhesion can still be as high as 62.5%, while the success rate of pregnancy will range between only 22.5 and 33.3% [11]. Therefore, establishing an anti-adhesion method that can promote the repair of endometrial injury is of great significance.

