### Sample size

The sample size calculation is based on the repair rate of moderate/severe IUA. Based on the fact that the repair rate of Foley balloon placement was 47–71.67% [8, 19], we assume that the effective rate of uterine adhesion repair can reach 80%. According to the calculation method for several cases related to the superiority study, the number of samples was estimated as 83, with *α* = 0.025 (one-sided) and *β* = 0.2. A sample size of 83 prospectively enrolled participants in each randomization arm. In consideration of a dropout rate of 20%, we will enroll 100 participants in each group response.

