### Statistical analysis methods

The data were analyzed using the R (v.2.1.1) tool. The measurement data were statistically presented in terms of mean ± standard deviation, maximum, minimum, mean 95% confidence interval, and median. A *t*-test was used for intergroup comparisons of data conforming to normality and homogeneity of variance, while a nonparametric test (chi-square test) was used for intergroup comparisons of data that did not conform to normality. The enumeration data were statistically represented by frequency (composition ratio). A rank–sum test was used for ordinal categorical variables, and the chi-square test was used for nominal categorical variables. Two-tailed tests were used for all statistical analyses, and a *P*-value of less than or equal to 0.05 was considered statistically significant for the tested difference.

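### AFS severity, scored before allocation and described as prognostic, is used neither in the described randomisation nor in the stated test, so some precision on the primary outcome is given up

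*Protocol article*

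**What the plan says.** All places are in the Protocol article.

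- **Randomization and allocation.** Allocation is 1:1. "Random numbers are generated by Excel, which will generate a random number table"; the assignments then go into coded, sealed, opaque envelopes. AFS is scored once the hysteroscope is in the cavity, and one trigger covers both grades: "If the uterine cavity was assessed as reflecting moderate or severe uterine cavity adhesion, the itinerant nurse opened the envelope with the corresponding number". Strata, blocks and minimisation are not mentioned.
- **Experimental design, Table 1.** Moderate is 5–8 points and severe is 9–12.
- **Primary outcome measures.** Effective repair is a fall of at least 4 points in total AFS. It is summarised as one response rate per group, pooled over grades.
- **Statistical analysis methods.** "the chi-square test was used for nominal categorical variables". No stratum or covariate is named.
- **Background.** In severe disease, "the recurrence rate of postoperative adhesion can still be as high as 62.5" per cent. The Discussion repeats that severe cases regenerate poorly and recur often.
- **Sample size.** "the repair rate of Foley balloon placement was 47–71.67" per cent, and "we assume that the effective rate of uterine adhesion repair can reach 80" per cent. The result is 83 per arm, or 100 with dropout.

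**The concern.** A variable that the article itself treats as prognostic is known for every woman before her envelope is opened, but it serves only to decide entry. If severe cases fall unevenly between the arms by chance, the crude difference in response rates carries that imbalance. Even with balanced arms, a crude test leaves the variation explained by severity in the error term. What is at stake is precision, and how convincing the primary result is if a baseline table shows uneven severity.

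**Working it through.** **1. Planning figure.** The article gives a range for the control rate, not a value. At 60% v 80%, one-sided 0.025, 80% power, pooled formula:

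n = [1.96·√(2·0.7·0.3) + 0.8416·√(0.6·0.4 + 0.8·0.2)]² / 0.20² = (1.270 + 0.532)² / 0.04 ≈ 81.2, so 82 per arm.

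This is close to the stated 83. The 60% is therefore back-solved and is used below as an assumption.

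**2. How severity enters the endpoint.** There are two routes, and they pull in opposite directions.
- Poorer regeneration lowers response in severe cases (Background).
- The 4-point rule raises it. Under Table 1 any residual adhesion scores at least 1 + 1 = 2. A woman entering at 5 must reach 1 or less, which means no adhesion and normal menses. A woman entering at 12 qualifies at 8, while still graded moderate.

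The net size and sign are not in the article, so a range is needed.

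**3. How often imbalance arises.** The SD of the difference in severe share is √(2s(1−s)/n). With half the women severe (assumed) and n = 100 this is √(0.5/100) = 7.1 points. An imbalance of at least 10 points has an exact binomial probability of 0.18.

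**4. Shift in the crude difference for a 10-point imbalance.** Split evenly between the arms, shift = 0.10 × (control gap + experimental gap)/2. Experimental rates come from a common odds ratio that gives 80% overall.

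| Severe share | Control, moderate/severe | Experimental, moderate/severe | Shift |
|---|---|---|---|
| 50% | 72.5/47.5 (gap 25) | 88.2/71.8 (gap 16.3) | 0.10 × 41.3/2 = 2.1 points |
| 30% | 69.6/37.5 (gap 32.1) | 87.0/63.7 (gap 23.4) | 0.10 × 55.5/2 = 2.8 points |
| 50% | 82.5/37.5 (gap 45) | 93.9/66.1 (gap 27.8) | 0.10 × 72.8/2 = 3.6 points |

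Against a planned difference of 20 points these are 10%, 14% and 18%.

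**5. Power, by simulation.** Unstratified allocation, half severe, 60% v 80%, one-sided 0.025. CMH is the Cochran-Mantel-Haenszel test stratified by grade.

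| Control gap | 83 per arm: crude → CMH | 100 per arm: crude → CMH |
|---|---|---|
| 10 | 81.3% → 81.2% | 87.8% → 87.8% |
| 20 | 81.5% → 82.4% | 87.9% → 88.7% |
| 30 | 81.3% → 83.8% | 88.0% → 90.0% |
| 40 | 81.3% → 86.2% | 87.9% → 91.7% |

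At 80 per arm, a 25-point gap gives about 80% → 81.5%, a 45-point gap 80% → 86%, and the 30%-severe case in step 4 80% → 83%.

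**6. Type I error.** Across these scenarios the crude test after unstratified allocation stays at 0.024–0.027 one-sided. If allocation is stratified and the test stays crude, it falls to about 0.015 at a 40-point gap, which is conservative.

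**The case against.** **Validity.** Simple 1:1 randomisation with an unadjusted comparison is valid, and the standard error already allows for chance imbalance. This stands. A reader might infer that the primary result is biased or that false positives are inflated; step 6 shows neither.

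**Silence in a condensed article.** The article never uses the word unstratified, and an adjusted analysis could sit in a fuller document. This stands in part. The absence of strata is inferred from a description of one table and one trigger. The analysis section does, however, state a test, and a better one is available from data already collected. It assigns no test to the primary outcome by name; chi-square is the natural reading for a response rate.

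**Size.** A reader might take the Background figure at face value: severe repair 100 − 62.5 = 37.5%, half the women severe, hence a 45-point gap, a shift of 0.10 × 45 = 4.5 points (22% of the effect) and power of 86% instead of 80%. The article does not support that as the expected case.
- The 62.5% is an upper figure, and it is for recurrence, which is not the complement of a 4-point fall.
- The scenario forces moderate control repair to 82.5%, above both the cited balloon ceiling of 71.67% and the 80% assumed for repair.
- The 4.5 points apply the control gap to the whole imbalance, although the gap is smaller in the experimental arm.

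**Direction.** Because the two routes in step 2 oppose each other, it cannot be said outright that power is lost.

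**Conclusion.** The concern holds as a modest, low-cost improvement. Severity is known before allocation, is called prognostic, and appears in neither the described randomisation nor the stated test. The consequence is a possible shift of about 2 to 4 points in a single trial's estimate for a 10-point imbalance, at repair gaps of 25 to 45 points. Forgone power is about 1 to 3 points at gaps of 20 to 30, up to about 6 at 45, and near zero if the two routes cancel. These figures rest on assumptions that the article does not supply: 60% control repair, 30–50% severe, and a common odds ratio across grades. Most of the gain comes from the analysis, since CMH after unstratified allocation recovers nearly all of it.

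**What to change.** **Statistical analysis methods.** State that the primary response rate is compared by a Cochran-Mantel-Haenszel test stratified by the AFS grade recorded before the envelope was opened (5–8 or 9–12), and report the stratum-adjusted risk difference with 95% CI. A logistic model with baseline AFS, standardised to a risk difference, would serve equally well. The cost is a sentence or two of wording, with no extra patients, visits or measurements.

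**Randomization and allocation, only if enrolment has not begun.** The statistician may also prepare separate concealed envelope sequences by grade, with randomly varied block sizes that are not disclosed to the operators. The costs are a second set of envelopes and some predictability of allocation, because operators see each assignment and a borderline 8 or 9 decides which sequence is drawn. Stratified allocation should not be paired with an unstratified chi-square. If enrolment has begun, keep the existing list and change only the analysis, before outcomes are compared by arm.
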